## Abstract

**Background:**

Bipolar disorder (BD) is characterized by recurrent (hypo)manic and depressive episodes, alternating with euthymic states in which patients are relatively symptom free. Besides clinical recovery, it is important to also strive for improvement of mental well-being and personal recovery. One prominent field focussing on the improvement of well-being is positive psychology. However, studies assessing the effects of positive psychology or personal recovery interventions for people with BD are scarce and have used weak methodological designs. The study described in this protocol article aims to assess the effectiveness of a multicomponent positive psychology intervention (“Living well with bipolar disorder”) adjusted for people with BD in the euthymic phase to improve well-being and personal recovery.

**Method:**

The study concerns a pragmatic randomized multicenter trial. The principle objective of the study is to assess whether the positive psychology intervention offered to BD patients in remission in addition to usual care (CAU) is more effective than CAU. The study will include 112 participants randomized to either the experimental condition receiving the intervention in addition to CAU or the control condition receiving CAU. The study population are patients with BD I or II in the euthymic phase.

The inclusion criteria are 1) diagnosis of BD I or BD II, 2) between the ages of 18–65, 3) four or more supportive sessions in the last year, and 4) only residual depressive or manic symptoms. Patients are excluded if they are in a depressive or manic episode, have current addiction problems or have optimal levels of well-being. Measurements take place at baseline, post-intervention and follow-up 6 and 12 months from baseline. Outcomes of measures include positive well-being, personal recovery, psychopathology, self-compassion, positive relationships, dampening of positive affect and relapse.

**Discussion:**

The outlined study will be the first RCT examining the effects of a multicomponent positive psychology intervention for patients with bipolar disorder. Several limitations, including generalizability of the results and possible attrition issues, are discussed in advance.

**Trial registration:**

This study has been registered in the Netherlands Trial Register (NTR6729) on 12 October 2017.

**Electronic supplementary material:**

The online version of this article (10.1186/s12888-018-1916-3) contains supplementary material, which is available to authorized users.

## Background

Bipolar disorder (BD) is a severe mood disorder and is characterized by recurrent (hypo)manic and depressive episodes, alternating with euthymic phases in which patients are relatively symptom free [1, 2]. BD is subclassified as bipolar I and bipolar II disorder. In the latter, patients solely experience hypomanic episodes but never a full manic episode [3, 4]. Prevalence estimates from the Netherlands reveal a lifetime prevalence of 1.3% and 12-month prevalence of 0.8% for BD I and II [5]. The economic burden in 2009 was estimated at 151 billion dollars per year in the United States [6]. BD is associated with decreased quality of life [7], negative social consequences, such as a disturbed social life and disrupted family interactions [8], issues related to work-performance and productivity [9, 10] and high caregiver burden [11, 12]. Current treatment for euthymic BD patients in the Netherlands includes pharmacotherapy, supportive treatment, psycho education and enhancement of self-management skills, and psychotherapy if indicated [13, 14].

In addition to current symptom-focused treatment, it becomes increasingly important to also focus on personal recovery [15–17]. Leamy, Bird, Le Boutillier, Williams and Slade [18] created a conceptual framework for personal recovery in mental health, containing five processes of personal recovery: connectedness, hope and optimism about the future, identity, meaning in life and empowerment (giving the acronym CHIME) as important factors for personal recovery [18]. Anthony (1993) operationalizes personal recovery in the context of psychopathology and describes it as the ability to live a meaningful, hopeful and contributing life, even in the presence of mental illness [19]. Similarly, Keyes [20] defines mental health recovery as the presence of well-being and not merely the absence of mental illness. Well-being, in turn, includes subjective well-being (i.e. positive affect and life-satisfaction), psychological well-being (i.e. meaning, goals in life, mastery, positive relationships) and social well-being (i.e. contributing to society) [20].

Personal recovery and well-being are particularly important in BD for several reasons. Residual subthreshold symptoms often persist in the interval between mood episodes [21–23]. Moreover, up to 35% of BD patients do not completely recover from a depressive or manic episode [24], which is an important risk factor for relapse [17]. Research also indicates that improvement of well-being protects against the recurrence of mental illness [25–27]. Patients with serious mental illness, such as BD also express dissatisfaction with current primary targets of treatment and instead argue for the importance of personal recovery outcomes [28, 29].

One prominent field of psychology focussing on the improvement of well-being and positive capacities is positive psychology [30]. Positive psychology interventions focus on the enhancement of positive feelings, behaviours, or cognitions and aim to improve well-being [31]. The key processes and goals of positive psychology are similar and central to personal recovery [15, 32] making positive psychology interventions potentially useful for improving both well-being and personal recovery in people with mental illness. The effect of positive psychology interventions has been shown in meta-analyses for both general and clinical populations [31, 33].

To date, however, no study has been conducted assessing the effect of positive psychology interventions for the treatment of people with BD and only a few studies investigated the effect of interventions focussing on the improvement of personal recovery. Deckersbach, Hölzel, Eisner, Stange, Peckham, Dougherty, Rauch, Lazar and Nierenberg [34] report on a small uncontrolled clinical trial with 12 euthymic participants diagnosed with BD using Mindfulness-Based Cognitive Therapy (CBT). Analysis from pre- to follow-up indicated significant moderate to large improvements in outcomes of depressive symptoms (Cohen’s *d* = .75), positive affect and aspects of well-being. Eisner, Eddie, Harley, Jacobo, Nierenberg and Deckersbach [35] conducted a proof-of-concept pilot study with 37 participants with BD who did not have a current major depressive, manic or mixed episode. Significant large improvements were obtained from baseline to post-treatment in psychological well-being, emotion regulation, and emotion reactivity. Finally, Jones, Smith, Mulligan, Lobban, Law, Dunn, Welford, Kelly, Mulligan and Morrison [36] investigated the effectiveness of recovery-focused CBT in a randomized controlled pilot trial (*n* = 67) with care as usual as control. Personal recovery significantly improved from baseline to 6 and 12 months follow-up (*d* = .62) in comparison with a control group receiving treatment as usual. Although no significant effects were obtained in average mood symptoms, patients in the recovery-focused CBT group showed significantly longer time to relapse into depression or mania over a 15-month period compared to patients only receiving care as usual. For example, 32 patients relapsed to either depression or mania (20 CAU v. 12 recovery-focused CBT) and median survival times were longer for recovery-focused CBT (56 weeks) compared to CAU (18 weeks).

In summary, no studies exist investigating the effectiveness of positive psychology interventions for BD patients. Furthermore, studies examining the effect of interventions aimed to enhance personal recovery or well-being for patients with BD are scarce and mostly used underpowered and weak methodological designs. For this reason, we aim to develop, implement and thoroughly investigate the effects of a multicomponent positive psychology intervention for the improvement of well-being and personal recovery for people with BD in an adequately powered randomized controlled trial. This will be the first study specifically evaluating a positive psychology intervention for patients with BD and will use a more sophisticated methodological design than studies before.

The primary objective is to evaluate the effectiveness of an eight-week multicomponent intervention *“*Living well with bipolar disorder*”* added to usual care (CAU) in BD patients in the euthymic phase. Primary outcome is the short and long term improvement of well-being and personal recovery. Secondly, the study aims to investigate whether the intervention in addition to CAU is more effective in improving social participation, and in improving depressive, manic, and anxiety symptoms. Thirdly, we will explore possible working mechanisms for intervention effects, including positive emotions, self-compassion, positive relationships and dampening of positive affect. Fourthly, the study aims to assess whether the intervention combined with CAU is more effective than CAU in reducing recurrence of depressive and (hypo)manic episodes in patients with BD in the long term. Finally, we aim to evaluate the cost-effectiveness of the intervention in addition to CAU for the treatment of euthymic patients with BD compared to CAU.

## Method

### Study design

A pragmatic, parallel-group randomized non-blinded multicenter trial is used to investigate the effectiveness of a multicomponent positive psychology intervention to improve well-being and personal recovery in patients with BD. Since the outcome in BD I and BD II disorder may be different, the sample will be stratified accordingly. Patients in the experimental condition receive “Living well with bipolar disorder” in addition to CAU. Participants in the control condition receive CAU only. Both participants in the control and experimental condition receive CAU according to the Dutch multidisciplinary guideline for BD [13], consisting mainly of self-monitoring of mood and supportive group sessions focusing on functional problems, and psychopharmacotherapy. The study duration is 12 months for each individual and includes five measurement points. Immediately prior to the start of the intervention a baseline measurement is completed (T0), 4 weeks after the start of the intervention a mid-treatment measurement takes place (T1) and immediately following the intervention a post measurement will be conducted (T2). In addition, two follow-up measures will be conducted, 6 months (T3) and 12 months after baseline (T4). Figure 1 shows the intended flow of participants (Additional file 1).

**Fig. 1 Fig1:**
[figure not shown]
Participant timeline

### Participants, eligibility and screening

In order to be eligible to participate in this study, participants must meet the following inclusion criteria: (1) diagnosis of BD I or BD II (assessed using the MINI-international neuropsychiatric interview [37]); (2) between the ages of 18–65; (3) four or more supportive sessions in the previous year with a psychiatrist or psychologist; and (4) presence of residual subsyndromal symptoms. Participants are included if they score between 2 (*minimal symptoms)* and 4 (*moderate symptoms*) for depressive symptoms and between 2 (*minimal symptoms*) and 3 (*mild symptoms*) for manic symptoms on the Clinical Global Impression Scale – Bipolar (CGI-BP). Exclusion criteria are: (1) currently in a depressive or (hypo)manic episode; (2) currently in treatment for addiction problems, or (3) having already optimal levels of well-being. Participants are assumed to have an optimal level of well-being if they score 4 or 5 on at least one item of the emotional well-being subscale together with a score of 4 or 5 on at least 6 of the 11 remaining items of the Mental Health Continuum-Short Form (MHC-SF; [20]).

### Randomization and treatment allocation

Randomization will be centrally conducted by the principal investigator using stratified (by center) block randomisation. For this purpose, randomization lists will be generated beforehand (one list for each participating treatment center) with an online tool (https://sealedenvelope.com/). The lists contain a random sequence of treatment allocations (i.e., participants are either allocated to the intervention or control condition according to the corresponding record) and are divided in blocks of allocations (20 allocations per block). By using blocks of allocations, 20 participants can be allocated to either the intervention or control condition after which the following block is used. This ensures that the group sessions in each center can start as soon as sufficient participants are randomized. The first participant included in the study is allocated according to the first record on the list, the second participant according to the second record on the list and so forth.

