### Study procedure

Initial screening for participation will be performed by therapists working at the treatment centers. To assess symptom severity of possible participants, the Clinical Global Impression Scale – Bipolar (CGI-BP) is used. After possible participants sign the informed consent, the principal investigator contacts the patient and agrees on a time and date to conduct the additional screening. To verify the diagnosis of BD, the MINI international neuropsychiatric interview [37, 57] is used and to assess well-being, participants are asked to complete the Mental Health Continuum – Short Form (MHC-SF) [58]. Eligible participants are then asked to complete the first test battery at baseline. Since the MHC-SF has already been completed for screening reasons before, participants are not asked to complete it again at baseline. Baseline measurements should take approximately 40 min to complete. Afterwards, allocation of participants to the intervention or control group takes place.

The first intervention group will start approximately in fall 2018 and the last group will finish in fall 2019. Four weeks after the intervention begins (T1) and after the intervention has finished (T2), participants in the intervention and control condition are asked to fill out a test battery again. Six (T3) and 12 (T4) months after baseline, participants in the experimental and control group will be asked to complete the follow-up measures. We assume that completing the test battery takes approximately 35 min on average at each measurement point. At T4, participants will be approached for a semi-structured telephone interview with the goal to retrospectively assess relapse into mood episodes in the past 9 months. To perform the interviews, a guideline will be prepared and the interviews will be conducted by student assistants according to a fixed scheme. The trained student assistants are blind to the treatment condition of the participants. One interview will take approximately 30 min.

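### Concealment of allocation from the enrolling investigator is not assured, and T0 cannot fall immediately before the intervention for patients who wait for a group to fill

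*Protocol article*

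**What the plan says.** Allocation. Under Randomization and treatment allocation: "Randomization will be centrally conducted by the principal investigator using stratified (by center) block randomisation". The method is given in some detail: "randomization lists will be generated beforehand (one list for each participating treatment center) with an online tool", which "are divided in blocks of allocations (20 allocations per block", with each new participant taking the next record. Under Study procedure, therapists at the centres do the first screening with the CGI-BP. After consent, "the principal investigator contacts the patient and agrees on a time and date to conduct the additional screening". That second screening consists of the MINI and the MHC-SF, which decide the diagnosis criterion and the well-being exclusion. Study design calls the trial non-blinded.

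Timing. Study design says: "Immediately prior to the start of the intervention a baseline measurement is completed (T0". Study procedure has eligible patients complete the baseline battery first and be allocated afterwards. On group starts, the randomisation section says of the block scheme: "This ensures that the group sessions in each center can start as soon as sufficient participants are randomized". The section on intervention adjustments sets groups at 8–10 people. In both arms T1 is four weeks after the intervention begins and T2 is after it ends. For the later visits, "two follow-up measures will be conducted, 6 months (T3) and 12 months after baseline (T4". For the primary outcome, "Since the MHC-SF has already been completed for screening reasons before, participants are not asked to complete it again at baseline".

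**The concern.** Two separate weaknesses meet in the enrolment procedure.

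The first is one of roles. Whoever holds an ordered list knows the next assignment. If the same role also has contact with the patient before eligibility is settled, it can influence whether and when that patient enters. Almost all outcomes are self-reported and the trial is open, so blinded assessment would not make up for selective entry.

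The second is one of time. Sequential allocation after baseline, combined with groups that wait to fill, opens a gap between T0 and the first session. The gap is long for the first patient in a block and short for the last. With two different anchors, a visit labelled 6-month follow-up is taken at different distances from the programme in different patients, and its effect averages over those distances. The MHC-SF value that serves as baseline is at least as old as the rest of T0.

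**Working it through.** **Roles, side by side.** List generated beforehand; records used in order; allocation by the principal investigator; contact for the eligibility-deciding screening by the principal investigator. Neither the randomisation section nor Study procedure places a separate person or a locked system between the list and enrolment.

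**Does the block size matter for prediction?** Assume 1:1 allocation within a block of 2b, with all past assignments known.
- Expected correct guesses = b + (2^(2b)/C(2b,b) − 1)/2. For b = 10: 10 + (1,048,576/184,756 − 1)/2 = 12.3 of 20, or 61.7%.
- Expected fully determined assignments = 2b/(b+1) = 20/11 = 1.8 of 20, or 9.1%.
- For blocks of 4 the same formulas give 70.8% and 33.3%.

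Blocks of 20 are therefore harder to predict than small blocks. For someone who can read the list, the figure is 100% at any block size. The weakness is access to the list.

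**How many randomisations fill a group?** With 10 intervention places among 20, the j-th intervention patient has expected position j × 21/11. For 8 patients this is 15.3 and for 10 it is 19.1. Simple doubling gives 16–20.

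**Total used below.** The planned 112 reproduces: the two-sided t-test at d = 0.60 and 80% power needs 44.6, so 45 per arm, and 90/0.80 = 112.5. It is not in dispute here.

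**Length of the wait.** The article gives no recruitment pace, so this is an assumption: even intake at four centres over 6 months.
- Rate: 112/4 = 28 per centre; 28/6 = 4.67 per month.
- Time to enter 16–20 patients: 16/4.67 = 3.4 to 20/4.67 = 4.3 months. Counting the gaps between patients takes off about 0.2 months.
- Programme length: 56 days/30.4 = 1.84 months.
- First in block, T3 minus programme end: 6 − 3.4 − 1.84 = about 0.7 months after, to 6 − 4.3 − 1.84 = about 0.1 months before.
- Last in block: 6 − 1.84 = about 4.2 months after.

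**Range.** A simulation of even intake over 8–12 months with four or six lists gave a wait of 3.8–11.0 months for the first intervention patient in a block and 1.9–5.5 months averaged over the group. Clustered intake would shorten all of these.

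**What the article's own schedule implies.** The relapse interview at month 12 looks back 9 months and is meant to cover the time after the intervention. The programme must then end by about month 12 − 9 = 3, which allows a wait of about 3 − 1.84 = 1.2 months. Recruitment opens in September 2018 and the first group starts in fall 2018, so the first fill is expected within roughly 3 months. With waits from 0 to 3 months, T3 would still fall between 6 − 3 − 1.84 = 1.2 and 4.2 months after programme end.

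**The case against.** The strongest reply is that this is a condensed article. Randomisation is described as central, custody of the list is often left to the full protocol, and nothing says that the list is open. The article says the principal investigator arranges the second screening, not that the same person conducts it. Discretion is also limited: the well-being exclusion is a fixed scoring rule on a self-report form, diagnosis rests on the MINI, therapists rate the CGI-BP, and allocation follows baseline. All of this stands. A reader might infer that allocation is not concealed, or that the screener and the allocator are one person; the text establishes neither. What remains is that the roles as stated put list and patient contact together, with no safeguard named.

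On timing, a reader might infer from even intake over 10–12 months that groups take 6–9 months to fill and that T3 often precedes the end of the programme. That fits poorly with a first group in fall 2018, a last group finishing in fall 2019, and the 9-month relapse window. The long waits are therefore not the planned case. The contradiction does not depend on them, because any wait breaks the stated timing of T0.

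A reader might also infer bias in the treatment comparison. T3 and T4 run from baseline in both arms and the wait is shared, so that does not follow. Nor is the T0 mark for the MHC-SF in Table 2 an error, since it is consistent with reusing the screening score.

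**Conclusion.** The point holds in two limited parts.

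1. Concealment from the enrolling investigator is not assured, because allocation from a pre-made ordered list and pre-eligibility patient contact are given to the same role. The block size of 20 is not the cause; it lowers predictability and matters only because filling a group takes time. Baseline is completed before allocation, so the risk is selective entry and not T0 scores coloured by knowledge of the arm. Its size cannot be computed from the article.

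2. The stated timing of T0 contradicts the enrolment sequence for early entrants in a block, and the mixed anchors make the interval from programme end to T3 vary. Under an assumed even 6-month intake at four centres, that interval runs from about zero to about 4 months. Under the shorter wait of up to 3 months that the start dates suggest, it runs from about 1 to 4 months. Slower even intake widens the spread and clustered intake narrows it. The consequence is a follow-up effect that is hard to interpret; the randomised comparison itself is not biased by the wait.

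**What to change.** Have each allocation released by the online service already chosen, or by a colleague without patient contact, and only after eligibility and T0 are locked. This needs a change of wording and no extra staff.

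For timing, preferably assemble a batch of ready, consenting patients per centre. Take T0 for all of them shortly before the group starts, including a fresh MHC-SF (14 items), then randomise the batch together and count T1–T4 in both arms from that one date. Rewrite Study design, Randomization and treatment allocation, and Study procedure so that they agree on when T0 occurs and what each visit is counted from, and check that the 9-month relapse window fits.

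The cost is that patients wait before randomisation instead of after it. Some may be lost, which does not harm the intention-to-treat comparison, and some may need their eligibility rechecked, which takes staff time. If batching is not workable, independent release of allocations plus corrected timing text is the minimum.
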